# Study Report

The Investigator will submit at least annual study reports to the reviewing HREC, or more frequent if required.

# Administrative Procedures

## Ethical Considerations

All documentation pertaining to the study must be prepared in accordance with the requirements outlined by the relevant ethics committee. All documentation must then be approved or given a favourable opinion in writing by an HREC as appropriate.

The Coordinating Principal Investigator is responsible for informing the HREC of any amendment to the protocol in accordance with local requirements. In addition, the HREC must approve all advertising used to recruit participants for the study.

The study will be performed in accordance with ethical principles that have their origin in the Declaration of Helsinki and are consistent with ICH/Good Clinical Practice, applicable regulatory requirements. The NHMRC National Statement on Human Research will also be utilised.

## Ethical Review Committee

The HREA and associated documents will be submitted for approval to the appointed HREC and written approval obtained from both the appointed HREC and Governance Office, before volunteers are recruited and participants are enrolled. The Coordinating Principal Investigator will submit the HREA and associated documents including Site Specific Applications to the appointed HREC and Research Governance. The Coordinating Principal Investigator has overall responsibility to ensure all reports are submitted in line with the appointed HREC reporting requirements.

## Informed Consent

Our criteria will ensure that recruited participants will be sufficiently competent to consent and participate in the study or to refuse consent. Current research provides evidence that while psychotic symptoms may be present, these do not robustly predict an individual’s functionality in daily life and capacity to make decisions, and whilst strongly correlated with cognitive impairment, do not reflect an enduring inability to understand information related to research participation.

## Participant Reimbursement

Participants will be reimbursed for out of pocket expenses, inconvenience and time involved by the provision of either prepaid gift cards (e.g. Coles-Myer, K-Mart etc) or a Garmin Vivofit wearable device (value ~ $80) at the beginning of the intervention, the choice will be theirs. We will provide a $20 gift card to those who verbally assent to complete the SEES questionnaire before and after a single session of exercise in week 3 of the intervention. We will provide a $40 gift card on completion of the baseline assessment and at the end of study assessment (total reimbursement $100). If the study is terminated by the Investigator prior to completion, or a participant withdraws or is withdrawn from the study before completion, a pro-rata payment will be made at the discretion of the Investigator.

Participants will be given an opportunity to participate in a small group interview at the end of the intervention and will be reimbursed a $20 gift card for inconvenience and time involved.

## Investigator Indemnification

The clinical trial insurance will reimburse participants for costs of medical care that occur as a result of complications directly related to participation in this study. The Investigator and insurance company will be notified as soon as possible if this occurs or where a causal relationship cannot be excluded. All SAE’s will be reported to the nominated Hospital and Health Service insurance company.

## Publication Policy

Results will be disseminated in peer reviewed publications and published in international journals. Only group data will be reported.

## Protocol Amendments

Any amendments to the protocol will be submitted to the appointed HREC by the Coordinating Principal Investigator for approval. Any approved amendments by the appointed HREC will be forwarded by the Coordinating Principal Investigator for submission to each Research Governance Office.

No changes (amendments) to the Protocol will be implemented without prior approval from the Reviewing Ethics Committee. If a Protocol amendment requires changes to the Informed Consent Form, the revised Informed Consent Form, prepared by the Coordinating Principal Investigator, will be approved by the Reviewing Ethics Committee and site governance officers.

Once the final Protocol has been issued and signed by the Coordinating Principal Investigator and the authorised signatories, it will not be informally altered. All protocol amendments will pass through appropriate approval steps before being implemented. Any change to the protocol constitutes an amendment.

Where the amendment affects the ongoing suitability of the study at a participating site, Research Governance approval will also be sought. The Research Governance Office will determine the ongoing suitability based on the amendment submitted.

The Coordinating Principal Investigator will submit the amendment to the appointed HREC for their approval; written approval will be obtained. Completed and signed Protocol amendments will be circulated to all appointed site Investigators.

## Version Control

Version control ensures that amendments to documents are tracked and verifiable and that the correct version of a document is in use according to the relevant ethical, regulatory or local approval.

All documents will be given a version number and date e.g. Version 1.0 15-Feb-15

Each amendment to a document will require a version number and date to be updated.

If this is a **significant change** e.g. change in the content of the document, then the version number will be increased by 1.0.

If it is a **minor change** e.g. contact details, then the number after the decimal point will be increased by 0.1.

## Protocol Compliance

Should there be questions or consideration of deviation from the Protocol, clarification will be sought from the Coordinating Principal Investigator. Any participant treated in a manner that deviates from the Protocol, or who is admitted into the study but is not qualified according to the Protocol, will be ineligible for analysis.

If an emergency occurs that requires a departure from the Protocol, the nature and reasons for the Protocol violation/deviation will be recorded in the CRF and the Coordinating Principal Investigator will notify the Reviewing HREC and /or Governance Office as soon as possible.

Whilst the Coordinating Principal Investigator has overall responsibility for the conduct of the study, the appointed site Investigators will have the responsibility to ensure all study personnel at their sites comply with GCP, National Statement on Ethical Conduct (2007), Australian Code for the Responsible Conduct of Research and local policies and procedures.

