**Feasibility Criteria**

Recruitment – percentage of participants who consent to the study as a proportion of CCU residents who are referred from the three sites. Recruitment into exercise trials for people with SMI can be highly variable, however > 50% (majority) will be considered feasible.

Retention – the proportion of participants consenting to the trial who complete follow up assessments at 8 weeks as a proportion of the total number allocated in each condition. Feasibility will be defined as > 65% based on previous research (49).

Participation – the number of supervised exercise sessions attended by participants in each condition (RT and AIT group) as a proportion of total available sessions (3 sessions per week for 8 weeks - 24); feasibility will be defined by attendance at greater than 60% of sessions (15 sessions).

Participants will be evaluated at baseline and end point week 8. Total duration of the study will be 8 weeks. All outcome raters will be blind to outcome allocation, however blinding of participants to their exercise condition will not be possible.

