# Participant Completion and Discontinuation

## Participant Completion

Participants are considered to have completed the study if they complete 8 weeks of intervention. The number of supervised exercise sessions attended by participants in each condition (RT and MIIT group) as a proportion of total available sessions (3 sessions per week for 8 weeks - 24); feasibility will be defined by attendance at greater than 60% of sessions (15 sessions).

Participants will be asked to complete post measures even if they are withdrawn from the study intervention, where possible.

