## Statistical Analysis

Data analyses will be conducted using SPSS Statistics 24, (SPSS Inc, Chicago, Illinois) for the primary outcomes. Continuous variables were summarized using means and standard deviations (SD) (or median and interquartile range for non-parametric data). All variables will be tested for normality using the Shapiro-wilks test, and visual inspection of Q-Q plots. Baseline demographic and clinical variables, participation and AE rates and mean aggregate acceptability scores will be compared between the two exercise groups using independent t-tests or Mann-Whitney U for non-parametric data. Chi square analysis for categorical data will be used to detect any baseline differences between the two exercise groups and for comparison of acceptability categories (strongly agree/agree versus other) per questionnaire item between the groups.

Baseline demographic and clinical variables will be compared between the 2 exercise groups using independent t tests (or Mann Whitney U tests if data non parametric) for continuous data and Chi2 square analysis for categorical data to detect any baseline differences between the 2 exercise groups. Baseline characteristics of those who complete >50% of the program will be compared to those who withdraw to identify characteristics of those who drop out.

To analyse the impact of the proposed exercise intervention on secondary outcomes, analyses will be performed on an intention-to-treat basis. Change from baseline in secondary outcomes at week 8 will be calculated as least squares (LS) means using a Linear Mixed Effects Model (LMM). Treatment group (RT or AIT) and time will be used as factors, with covariates established in previous similar research (age, gender, participation, and antipsychotic medication use),(García-Garcés et al., 2021b). Where group/time differences were detected, posthoc (Bonferroni) analyses will be carried out separately for the intervention and control group, with Cohen’s d estimate of effect sizes provided. LMM was performed using R (software version 4.04, 2024). All the statistical tests were two-tailed with the critical P value for significance set at?<?0.05.

For the RT group only, 12 RM strength will be assessed for normality and compared pre and post the intervention using paired samples t test.

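### Section 16.9 bars protocol deviators and unqualified entrants from analysis, which contradicts intention-to-treat for the secondary outcomes and the all-allocated denominator for primary retention

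*Protocol*

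**What the plan says.** Four places in the protocol bear on who is analysed.

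- **Section 16.9, Protocol Compliance.** The exclusion has two limbs: "Any participant treated in a manner that deviates from the Protocol", and anyone "who is admitted into the study but is not qualified according to the Protocol, will be ineligible for analysis". The sentence does not say which outcome or analysis set it governs.
- **Section 11.4, Statistical Analysis.** For the secondary outcomes, "analyses will be performed on an intention-to-treat basis".
- **Section 3, Feasibility Criteria.** Retention, one of the three primary criteria, is completion of the week 8 assessments "as a proportion of the total number allocated in each condition", with feasibility set at more than 65%. Participation is sessions attended out of the 24 available, with feasibility set at more than 60% (15 sessions).
- **Section 9.1, Participant Completion.** "Participants will be asked to complete post measures even if they are withdrawn from the study intervention, where possible".

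Nothing elsewhere in the protocol limits the section 16.9 rule to a per-protocol or sensitivity analysis.

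**The concern.** Whether people can follow the programme is part of what a feasibility trial measures. A rule that removes participants because their treatment departed from the protocol takes part of that result out of the data. For the secondary outcomes it also replaces the randomised groups with groups selected on what happened after allocation, which intention-to-treat is meant to prevent.

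With about 25 people per arm, a few exclusions move a percentage a long way. Because the protocol states both an inclusive and an exclusive rule, the population could also be chosen after the results are known. Safety is exposed too. Section 16.9 goes on to describe an emergency departure as a violation or deviation, so on a literal reading a participant managed in that way would drop out of the adverse-event comparison planned in section 11.4.

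**Working it through.** **1. Can the statements be followed together?**

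| Place | Who counts | Compatible with 16.9? |
| --- | --- | --- |
| 11.4, secondary outcomes | Intention-to-treat | No |
| 3, retention | All allocated, per condition | No |
| 3, participation | Sessions attended out of those available; population not spelled out | Affected, but no direct contradiction in words |
| 3, recruitment | Consents out of referrals | Not obviously affected |
| 9.1, week 8 measures after withdrawal | Data collection only | Yes, strictly; it shows an intent to keep such people in the data |

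**2. The plan's own figures.** Section 11.3 gives 50 participants, about 25 per arm, with 20% dropout: 2 × 25 = 50, and 50 × 0.80 = 40 completers, or 20 per arm. For participation, 0.60 × 24 = 14.4, so the smallest whole number above 60% is 15 (15/24 = 62.5%). Both figures reproduce. There is no power calculation to check.

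**3. Effect on retention.** Let c be the completers among 25 allocated and k the number excluded under section 16.9. The protocol gives no deviation rate, so c and k are assumptions; I took k from 1 to 5.

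- All kept: c/25
- Excluded people are all non-completers: c/(25 − k)
- Excluded people are all completers: (c − k)/(25 − k)
- Deviation unrelated to completion: c/25 on average

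| c | All kept | k | If all non-completers | If all completers |
| --- | --- | --- | --- | --- |
| 15 | 60.0%, fails | 2 | 15/23 = 65.2%, passes | 13/23 = 56.5%, fails |
| 15 | 60.0%, fails | 3 | 15/22 = 68.2%, passes | 12/22 = 54.5%, fails |
| 16 | 64.0%, fails | 1 | 16/24 = 66.7%, passes | 15/24 = 62.5%, fails |
| 17 | 68.0%, passes | 3 | 17/22 = 77.3%, passes | 14/22 = 63.6%, fails |
| 20 (planned) | 80.0%, passes | 3 | 20/22 = 90.9%, passes | 17/22 = 77.3%, passes |
| 20 (planned) | 80.0%, passes | 5 | 20/20 = 100%, passes | 15/20 = 75.0%, passes |

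The verdict can flip either way when an arm lies near 65%. It does not flip at the planned dropout.

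**4. Effect on participation.** Assume that the criterion is applied to the arm mean (the protocol does not say so), that mean attendance is 60%, and that 5 of 25 are excluded with mean attendance d. The remaining mean is (25 × 0.60 − 5d)/20.

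- d = 20%: (15 − 1)/20 = 70.0%
- d = 60%: (15 − 3)/20 = 60.0%
- d = 80%: (15 − 4)/20 = 55.0%

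Again the direction depends on who is removed.

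**The case against.** The best defence is that section 16.9 is general administrative text, that the specific sections on feasibility and analysis state the inclusive rule, and that the trial is exploratory. A sensible analyst would follow the specific sections. That lowers the chance of harm but does not remove the sentence. Section 16.7 says that the protocol is not to be altered informally, so any analysis plan would have to depart from one protocol statement or another.

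A reader might also infer more than the documents support.

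- **That the rule inflates retention and participation.** The protocol gives no deviation rate and no link between deviation and completion. Someone who breaks the outside-exercise restriction in section 6.1 may attend every session, and removing that person lowers the rates.
- **That poor attendance is itself a deviation, so all poor attenders are removed.** No section says so. The wording concerns how a participant is treated, and sections 3 and 11.4 handle attendance as an outcome to be analysed. Sections 7.1.1 to 7.1.4 also allow much individual tailoring, so varied session content is often within protocol.
- **That intention-to-treat is promised for the primary outcome.** Section 11.4 states it only for the secondary outcomes. For the primary outcome, the conflict is with the retention denominator alone.
- **That section 9.1 contradicts section 16.9.** Withdrawal is a pathway the protocol provides for, and collecting data does not conflict with a rule on who is analysed.

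It is also fair that the upward flips need an arm just under the threshold and excluded people who are non-completers.

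**Conclusion.** Wrong as written. The section 16.9 exclusion contradicts the intention-to-treat basis for the secondary outcomes and the all-allocated denominator for primary retention, and it leaves open which rule governs participation and safety. Followed literally, it can bias these results in either direction; upward bias requires that those excluded complete or attend less than the rest.

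In an arm of 25, one exclusion can turn a failed retention criterion into a pass (64.0% to 66.7%), and three can turn a pass into a failure (68.0% to 63.6%). These sizes rest on assumed counts of completers and deviators, with every excluded person of one kind. At the protocol's own 20% dropout the retention verdict stands for up to five exclusions, although the reported rate could range from 75.0% to 100% around the true 80.0%. The contradiction itself rests on no assumption.

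**What to change.** In section 16.9, delete the sentence that bars deviators and unqualified entrants from analysis, or restrict it to a per-protocol analysis labelled as a sensitivity analysis.

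In section 11.4, state that all randomised participants remain in their allocated arm for retention, participation, safety and the secondary outcomes, and that deviations and eligibility violations are logged and reported by arm.

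The cost is a short text amendment with ethics committee approval under section 16.7. No extra data collection is needed, because section 9.1 already seeks week 8 measures from people withdrawn from the intervention.

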## Archives: Retention of Study Records

All Case report Forms (CRF’s) and study documentation will be kept by the Investigators for at least 15 years or the maximum time frame as determined by local regulations, whichever is the longest.

